# 9. Management of adverse events

## 9.1.　 Definition of adverse events

### 9.1.1.　 Definition of adverse events

The term "Adverse Event" shall mean any unwanted or unintended injury or illness or its symptoms (including abnormal laboratory values) that occurs to a research subject, whether or not causally related to the research being conducted.

### 9.1.2.　 Definition of Serious adverse events

　 A serious adverse event (SAE) is an adverse event that falls under any of the following categories.

1. Deadly

2. Life-threatening

3. Requires hospitalization or prolonged hospitalization for treatment

4. Permanent or significant disability or dysfunction

5. Inheritance of congenital anomalies in offspring

## 9.2.　 Response to subjects when adverse events occur

When an adverse event is observed, the principal investigator or research assistant will immediately take appropriate measures and note this in the medical record. In addition, if the study treatment is discontinued due to an adverse event, or if treatment for the adverse event becomes necessary, the subject will be informed.

## 9.3.　 Evaluation and reporting of adverse events

When a serious adverse event is recognized, the research assistant will take necessary measures, such as explaining the event to the research subjects, etc., and promptly report the event to the principal investigator.

When the principal investigator recognizes the occurrence of a serious adverse event, he/she will promptly prepare a "Report on Serious Adverse Events (First Report)" (Shinshu University Medical Clinical Research Plan Form 4) and report it to the Dean of the Shinshu University of School of Medicine. The principal investigator should prepare a "Report on Serious Adverse Events (Second Report)" (Shinshu University Clinical Research Plan Form 5) and report it to the Dean of the Shinshu University School of Medicine within 7 days. In addition, the principle investigator will promptly share the information on the occurrence of the adverse event with the research assistants involved in the implementation of the research.

## 9.4.　 Predicted adverse events

The risk of developing exercise-induced locomotor disease, hypoglycemia, and hypotension is expected.

Adverse events reported for resistance exercise and aerobic exercise in 251 patients wity type 2 diabetes between 39 and 70 years of age, are as follows.

Hypoglycemia frequency 3% (no severe hypoglycemia), trauma frequency 8%, locomotor disorders (upper and lower extremity joint pain, back pain) frequency 17%^5)^.

# 10. Target number of enrolled cases: 70 cases

# 11. Statistical matter

The basic policy of the statistical analysis is shown below. The technical details of the statistical analysis will be specified separately in the statistical analysis plan.

## 11.1.　 Basis for setting the target number of cases to be enrolled

Since this study is an exploratory study, the number of cases was calculated based on feasibility.

Among new and follow-up patients with diabetes at our hospital, the number of patients considered to be eligible for the study is about 70 cases/month, of which we estimate that about 35 cases/month would fit the selection criteria and could be enrolled after obtaining consent.

## 11.2.　 Statistical analysis methods

## ・Primary endpoint：HbA1c

## ・Secondary endpoints：Liver fat mass by MRI, abdominal visceral fat and thigh muscle mass by CT, thigh muscle strength by EMG, BMI, VO2 peak (maximal oxygen uptake), insulin sensitivity (blood C-peptide, IRI), HDL cholesterol, LDL cholesterol, triglycerides, systolic blood pressure, mean blood glucose and variability (using FreeStyle Libre Pro), urinary albumin, changes in drug dosage from baseline (start) to 20 weeks, frequency of IWT and target achievement rate (at least 60 minutes/week of fast walking).

## Safety endpoints：Studies on adverse events (collected only for hypoglycemia and hypotension), serious adverse events (SAEs), and musculoskeletal disorders.

11.2.1.　 Overview of Analysis Objectives

1）Full analysis set (FAS): Participant population enrolled and with at least one analysis available, including baseline.

2）Per protocol set (PPS): Among participants corresponding to FAS, participant population with no significant protocol deviations that would affect the efficacy assessment.

### 3）Safety analysis set (SAF): population of participants who have received at least one protocol treatment.

### 11.2.2.　 Analysis on the primary endpoint (analysis population: FAS)

The percent change in HbA1c from baseline (start date) to 20 weeks in subject i is defined as follows. If HbA1c measurements at either or both time points are missing, the rate of change in HbA1c is considered missing.

$${HbA1c rate of Variation}_{i}=\frac{{HbA1c measurements}_{i,baseline}-{HbA1c measurements}_{i,20w}}{{HbA1c measurements}_{i,baseline}}$$

Estimate the mean and 95% confidence interval of the mean for the rate of change in HbA1c.

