## IWT is an exercise therapy in which fast walking (>70% of maximal oxygen uptake) and slow walking (<40% of maximal oxygen uptake) are performed for 3 minutes each, for a total of 5 sets (30 minutes)/day, at least 4 times a week. In this clinical trial, the target length of fast walking is set at 60 minutes/week. We would like to examine adherence to IWT, and so, except for participants who withdraw their consent, the study will continue even if the actual fast walking time is not enough. Eventually, all remaining participants will be evaluated after completion of the study. We will ask the participants to continue IWT as much as possible after the 20-week period until they have completed all the evaluation.

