8.2.　 Beginning and End Endpoints

・Body composition evaluation: liver fat content by abdominal MRI, abdominal visceral fat content by CT, thigh muscle mass by CT.

・Thigh muscle strength using isometric lower limb muscle testing equipment.

・Physical fitness measurement (using of JD Mate): VO2 peak (maximum oxygen uptake), target level value for training, maximum heart rate.

・Mean blood glucose and blood glucose variability（using of FreeStyle Libre Pro）

・Daily calorie consumption (using of JD Mate): calorie consumption, number of steps, measurement time (minutes)

・Dietary survey

・Concomitant medications: changes from start to end of diabetes medications (insulin, oral medications), hypertension medications, and lipid disorder medications.

・Insulin sensitivity*: blood CPR, IRI

・Blood tests*: HDL-C, LDL-C, triglycerides, BUN, Cre, eGFR, AST, ALT, fasting blood glucose, HbA1c.

・Urinalysis*: Urinary albumin (creatinine equivalent)

・Vital signs*: systolic and diastolic blood pressure.

・Body weight *

　*…Also evaluate at 4, 8, 12, 16, and 18 week visits.

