8.4.　 Post-End Assessment Items

・Surveys for adverse events (collected only for hypoglycemia and hypotension), serious adverse events (SAEs), and locomotor disorders.

Observation, Inspection and Reporting Schedule

|  | **screening** | **previous observation** | **Start Date** | **4 w** | **8w** | **12w** | **16w** | **18w** | **20w** | **after the end** | **time of cessation** |
| --- | --- | --- | --- | --- | --- | --- | --- | --- | --- | --- | --- |
|  |  |  | **baseline** | **±2w** | **±2w** | **±2w** | **-2w　+1ｗ** | **±1w** | **±2w** | **The items implemented from 20 weeks to 28 weeks of the start date.** |  |
| Patient Background | ○ |  |  |  |  |  |  |  |  |  |  |
| Body Composition Assessment |  | ○ |  |  |  |  |  |  |  | ○ |  |
| Physical fitness test |  | ○ |  |  |  |  |  |  |  | ○ |  |
| Interval fast walking |  |  |  |  |  | （20ｗ+ Until the end） |  |  |  |  |  |
| Dietary survey | ○ |  |  |  |  |  |  | ○ |  |  |  |
| Calorie consumption | ○(1w) |  |  |  |  |  |  | ○(1w) |  |  |  |
| BMI | ○ |  | ○ |  | ○ | ○ | ○ |  | ○ |  | (Weight only) |
| Insulin sensitivity |  |  | ○ |  |  |  |  |  | ○ |  |  |
| Blood test | ○ |  | ○ | ○ | ○ | ○ | ○ |  | ○ |  |  |
| Urinalysis | ○ |  | ○ |  |  |  |  |  | ○ |  |  |
| Blood pressure | ○ |  | ○ | ○ | ○ | ○ | ○ |  | ○ |  | ○ |
| Blood glucose level variation | ○(2w) |  |  |  |  |  |  | ○  (18~20w) | |  |  |
| concomitant medications |  |  | ○ |  |  |  |  |  | ○ |  | ○ |
| Survey on locomoter disorders |  |  | ○ | ○ | ○ | ○ | ○ | ○ | ○ | ○ | ○ |
| Adverse events |  |  |  |  |  |  |  |  |  | ○ | ○ |

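### The primary analysis carries the FAS label but is a completers mean: it needs a week-20 HbA1c and leaves the values from weeks 4, 8, 12 and 16 unused

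*Protocol*

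**What the plan says.** Section 11.2.1 defines the FAS as "Participant population enrolled and with at least one analysis available, including baseline". Whether baseline counts as the one available analysis or must be joined by another, a week-20 value is not required.

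Section 11.2.2 assigns the primary endpoint to the FAS. It defines each participant's value as the fall from baseline to week 20 divided by baseline, so a positive value is an improvement. Two sentences then fix the analysis: "If HbA1c measurements at either or both time points are missing, the rate of change in HbA1c is considered missing", and "Estimate the mean and 95% confidence interval of the mean for the rate of change in HbA1c".

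Section 8.2 puts HbA1c among the blood tests ("fasting blood glucose, HbA1c") and says of the starred items, which include them: "Also evaluate at 4, 8, 12, 16, and 18 week visits". The schedule in section 8 ticks the blood test at screening, baseline and weeks 4, 8, 12, 16 and 20. Week 18 appears in the text of 8.2 but not in the blood-test row. That should be reconciled, but it does not affect this point. The column headed "time of cessation" has no blood test.

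Section 5.3 keeps participants in the study when their walking time falls short, unless they withdraw consent, and adds: "Eventually, all remaining participants will be evaluated after completion of the study". Section 5.5 lists several ways in which study treatment can end.

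**The concern.** A participant who leaves after week 16 has a baseline and four later HbA1c values and belongs to the FAS, yet adds nothing to the primary mean. The result would be reported as a FAS estimate while describing only those who reached week 20.

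This matters if leaving is related to response. The protocol makes that plausible without establishing it. Section 2 attributes low uptake of exercise to motivation, time and habit. Section 9.4 cites locomotor disorders in 17% and trauma in 8% of an earlier exercise cohort. With a single arm there is no control group in which a similar bias might cancel, and this mean is the whole of the primary analysis.

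**Working it through.** **Is it a completers mean?** Under 11.2.2 a participant's value is missing unless baseline and week 20 both exist. The estimator is a plain mean, with no model and no imputation. A plain mean can use only non-missing values, so it runs over participants with both measurements. Section 11 leaves technical details to the SAP, but this rule and this estimator are written in the protocol itself.

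**Is there a figure to reproduce?** No. Section 11.1 sets 70 cases by feasibility, without effect size, SD, power or dropout rate. All sizes below rest on assumptions.

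**Direct calculation.** Let *d* be the dropout proportion, *m_c* the mean percent fall in completers and *m_l* the mean in leavers.

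- True mean = (1 − d)·m_c + d·m_l
- Bias of the completers mean = d·(m_c − m_l)

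For illustration, m_c = 0.46 / 7.5 × 100 = 6.13%. The 0.46 points is the aerobic-exercise difference from control quoted in section 2, which is not a design assumption. The baseline of 7.5% is assumed. Bias is in percentage points; the figure in brackets is relative to the true mean.

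| Dropout | In the mean, of 70 | True mean, leavers at 0 | Bias | True mean, leavers at half of m_c | Bias |
|---|---|---|---|---|---|
| 5% | 66 | 5.83 | 0.31 (5%) | 5.98 | 0.15 (3%) |
| 10% | 63 | 5.52 | 0.61 (11%) | 5.83 | 0.31 (5%) |
| 20% | 56 | 4.91 | 1.23 (25%) | 5.52 | 0.61 (11%) |
| 30% | 49 | 4.29 | 1.84 (43%) | 5.21 | 0.92 (18%) |

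With leavers at zero the relative overstatement is d/(1 − d), whatever m_c is. If leavers do as well as completers, the bias is zero.

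For scale, with an assumed SD of percent change of 10, the 95% half-width is 1.96 × 10/√70 = 2.34 points with all 70 and 1.96 × 10/√56 = 2.62 with 56. At these dropout rates the bias is smaller than the sampling error, but a confidence interval does not account for it.

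**Simulation.** 600 trials per scenario of 70 participants, visits at weeks 0, 4, 8, 12, 16 and 20. Assumed: baseline 7.5% (SD 0.8), mean change −0.46 points (SD 0.7) reached by week 16, visit error SD 0.15. From week 8 on, leaving depended on the last observed change. The likelihood analysis was a joint normal model for baseline and percent change at every visit.

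| Who leaves | Dropout | Full data | Completers | Likelihood, all visits |
|---|---|---|---|---|
| Unrelated to response | 14.8% | 6.18 | 6.18 | 6.17 |
| Poor responders | 11.6% | 6.17 | 6.91 | 6.18 |
| Poor responders | 21.2% | 6.16 | 7.53 | 6.16 |
| Poor responders | 32.6% | 6.14 | 8.34 | 6.16 |
| Good responders | 39.5% | 6.12 | 3.25 | 6.11 |

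The three poor-responder rows overstate by 6.91/6.17 = 12%, 7.53/6.16 = 22% and 8.34/6.14 = 36%. They imply a strong contrast. At 21.2%, leavers average about (6.16 − 0.788 × 7.53)/0.212 ≈ 1.1%, against 7.5% in completers. Leaving was generated from observed HbA1c, so the likelihood analysis recovers the full-data mean by construction. The table does not show how it would do if leaving depended on unobserved values.

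**The case against.** The strongest reply is that the study is exploratory, sized by feasibility, and estimates a mean with no test or success threshold. No decision turns on this rule, and an uncontrolled before-after change could not be attributed to IWT under either estimator. A sensitivity analysis could sit in the SAP. This stands as an argument about severity. It does not alter the fact that the protocol fixes the primary rule, which a sensitivity analysis would leave in place.

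Four stronger readings are tempting, and the protocol does not support them.

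- *That the rule contradicts section 5.3.* That section speaks of remaining participants and excepts those who withdraw consent. Averaging those measured at week 20 is compatible with it. Section 5.3 in fact helps, because short walking time alone does not end participation.
- *That whoever stops IWT gives no final HbA1c.* The cessation column has no blood test, but nothing says that stopping cancels the week-20 visit, which has one. Section 5.5 also says that a temporary interruption is not a discontinuation. The protocol is unclear here; it does not exclude the measurement. A value taken at cessation would in any case not be a week-20 value under the stated rule.
- *That the interim values are thrown away.* They are absent from the primary estimate only. Section 11.2.3 allows open-ended exploratory modelling.
- *That the benefit is overstated.* Section 5.5 includes relocation and ineligibility, which need not follow response. The direction depends on who leaves.

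**Conclusion.** The point holds as a moderate one. The analysis labelled FAS is a completers mean, and HbA1c scheduled at four interim visits plays no part in it. Bias arises only if loss is related to response, and its sign depends on whether poor or good responders leave. If leavers have no change at all, the overstatement is about 5%, 11% and 25% of the true mean at 5%, 10% and 20% dropout. If leavers do half as well as completers, it is 3%, 5% and 11%. These figures rest on assumed dropout rates and an assumed gap between leavers and completers, since the protocol supplies neither. Retaining low adherers under section 5.3 should lower the loss, but the exits in section 5.5 remain. A reader might infer that the reported effect will be inflated; the protocol supports only that the estimator has no protection against it.

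**What to change.** In section 11.2.2, replace the rule and the simple mean with a repeated-measures likelihood model:

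- outcome: percent change in HbA1c at weeks 4, 8, 12, 16 and 20, each computed against baseline with the existing formula;
- terms: visit as a factor and centred baseline HbA1c as covariate, with unstructured covariance;
- participants: everyone in the FAS with a baseline and at least one later value;
- primary estimate: the week-20 mean with 95% confidence interval.

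The model should be on percent change. A week-20 minus baseline contrast on raw HbA1c would estimate absolute change, which is not the endpoint defined in 7.1 and 11.2.2. Carrying the last value forward is no substitute: in the simulation it gave 5.8% against 6.2% even when loss was unrelated to response.

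Keep the completers mean as a sensitivity analysis. Report how many week-20 values are missing and why. State in the schedule that the week-20 HbA1c is still collected from anyone who stops IWT without withdrawing consent.

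The cost is protocol and SAP wording, and follow-up to an already scheduled blood test for those who stop. The model assumes that data are missing at random given the observed HbA1c, and it cannot use participants who have a baseline only. Both limits should be stated with the result.

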### 11.2.3.　 Analysis on secondary endpoints (analysis population: FAS)

### 1）Descriptive summary

## Depending on the data type of each variable, appropriate summary statistics, contingency tables, figures, etc. should be used to summarize the data.

## 2) Exploratory data analysis

Statistical modeling is used to examine the quantitative nature of the following relationships (before -> after).

① Interval fast walking → Outcome

② Background/Baseline → Adherence to interval fast walking

For example, when considering glycemic control for ①, the frequency of IWT (a continuous variable such as hours per week) can be regressed against the achievement of the threshold for change in HbA1c (a binary variable of whether it is less than 7%) in a logistic model to estimate the frequency of IWT required to achieve a given percentage of achievement. ② can be expressed as the weight (influence) of each background/baseline factor with respect to appropriately defined adherence by methods such as regression or search trees.

Not limited to these examples, this analysis will be considered on an exploratory basis. Since specific consideration of models may require data review, it is acceptable to document the model identification at the time of reporting the analysis results, not necessarily in advance.

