# 2. Background and rationale

In a survey by the Ministry of Health, Labor and Welfare in Japan, the estimated number of adults with suspected diabetes increased to 10 million in 2016, and diet and exercise therapy are important for prevention and treatment of type 2 diabetes.

It has been reported that exercise therapy in diabetes patients improved insulin resistance in skeletal muscle and also reduced liver fat mass^1^.

It has also been suggested that exercise therapy is effective in improving HbA1c levels in patients with diabetes (Aerobic exercise group showed -0.46% reduction in HbA1c compared to the control group, resistance exercise group showed -0.37% reduction in HbA1c compared to the control group, and aerobic exercise group + resistance exercise group showed -0.96% reduction in HbA1c compared to the control group)^2^.

With alarming of sarcopenia (muscle weakness) in patients with diabetes, exercise therapy is important even for elderly diabetic patients. In reality, the implementation rate of exercise therapy is low. This is due to a variety of reasons, including patient motivation, time constraints, and lack of habit. Further, it is difficult for medical professionals to instruct patients on exercise therapy because there is no well-established method of exercise therapy for patients with diabetes. IWT "(walking at 70% or more of maximum fitness and walking at 40% or less of maximum fitness alternately for 5 to 10 sets/day for 3 minutes each, repeated at least 4 days/week)" is established by the Department of Sports Medical Sciences, Shinshu University Graduate School of Medicine. There is a report that IWT in patients with diabetes resulted in weight loss (-0.7 kg in a general exercise therapy group and -4.2 kg in IWT group) and a decrease in average blood glucose in CGM (+2 mg/dl in a general exercise therapy group and IWT group -12 mg/dl)^3^. One of the reasons for the effectiveness is the high level of adherence. Another reason may be that IWT allows patients to perform both aerobic and resistance exercise at the same time^4^。

However, there are no papers in Japan evaluating the effectiveness of IWT for patients with type 2 diabetes mellitus.

Therefore, we would like to evaluate blood glucose control and changes in body composition in patients with type 2 diabetes by performing IWT.

We would also like to examine the required amount of IWT to achieve the goal of HbA1c less than 7% in patients with diabetes.

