## 5.2.　 Research outline

## The target enrollment number is 70 patients.

## After enrollment, patients will undergo physical fitness measurements, imaging tests (simple CT of the abdomen and the thighs, and simple MRI of the abdomen), and evaluation of blood glucose variability using FreeStyle Libre Pro, followed by 20 weeks of IWT.

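### The only model illustrated for the required amount of IWT cuts HbA1c at 7%; a continuous regression would answer the same exploratory question more precisely

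*Protocol*

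**What the plan says.** The last line of Protocol section 2 states a wish to "examine the required amount of IWT to achieve the goal of HbA1c less than 7% in patients with diabetes". The objective section does not repeat it.

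The matching analysis is in section 11.2.3 2). As an example, weekly IWT is related to "the achievement of the threshold for change in HbA1c", defined as "a binary variable of whether it is less than 7%) in a logistic model to estimate the frequency of IWT required" for a given percentage of patients to achieve it. The sentence speaks of change, but below 7% is a level. I read it as the HbA1c level at week 20. The example names no regressor other than IWT.

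The same section keeps the choice open: "Not limited to these examples, this analysis will be considered on an exploratory basis". It also allows the model to be documented when results are reported.

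Section 11.2.2 keeps HbA1c continuous for the primary endpoint: "Estimate the mean and 95% confidence interval of the mean for the rate of change in HbA1c". On size, section 5.2 says "The target enrollment number is 70 patients", and section 11.1 explains: "Since this study is an exploratory study, the number of cases was calculated based on feasibility".

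**The concern.** HbA1c is measured on a continuous scale. After the cut, a fall from 9.5% to 7.1% counts the same as no change, and a move from 7.05% to 6.95% counts as full success. The 7% goal does not require this in the fitted model, because the chance of being below 7% at a given amount of walking can be read from a continuous regression and its residuals.

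The loss matters more here than in an ordinary comparison. A required amount is an inverse estimate, the distance to a threshold divided by a slope. Its 95% Fieller interval is bounded only when the slope differs from zero at the 5% level. With a sample size set by feasibility, lost information leads directly to wider or unbounded intervals for the quantity the aim asks for.

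**Working it through.** There is no power or precision figure to reproduce, since N = 70 rests on feasibility.

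**Step 1: loss from the cut alone.** For a normal outcome cut so that a share p falls below the threshold, the information kept is φ(z)² / [p(1 − p)], where z is the normal quantile of p.

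- p = 0.5: 0.3989² / 0.25 = 0.64
- p = 0.3: 0.3477² / 0.21 = 0.58
- p = 0.2: 0.2800² / 0.16 = 0.49
- p = 0.1: 0.1755² / 0.09 = 0.34

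So 36% is lost at 50/50 and 51% at 20/80. In patients, 0.64 × 70 ≈ 45 and 0.49 × 70 ≈ 34.

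**Step 2: loss in the slope comparison.** The inputs from the Protocol are N = 70, entry HbA1c 6.5 to 10.0% (section 4.1) and target fast walking 60 min/week (section 5.3). The rest is assumed: baseline HbA1c normal with mean 7.5 or 8.0 and SD 0.8, truncated to the entry range; walking SD 30 min/week; slopes of 0.3, 0.5 or 0.9% HbA1c per 60 min/week; residual SD 0.5 or 0.8. The effects of −0.46% and −0.96% cited in section 2 are group differences, not dose slopes, so they only show the order of magnitude.

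Information kept is the squared z of the IWT slope, logistic over linear, from 200,000 simulated patients per setting:

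- neither model adjusted for baseline: 36 to 61%
- both adjusted: 21 to 52%, so 48 to 79% is lost

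**Step 3: power at N = 70, both models adjusted for baseline.** Week-20 HbA1c = 7.1 + 0.8 × (baseline − 7) − slope × (min/60) + normal error; baseline mean 7.5, SD 0.8; 800 to 2,000 trials per setting; logistic test by likelihood ratio.

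| Slope per 60 min/week | Residual SD | Continuous | Cut at 7% |
|---|---|---|---|
| 0.2 | 0.8 | 0.18 | 0.12 |
| 0.3 | 0.6 | 0.51 | 0.30 |
| 0.4 | 0.6 | 0.76 | 0.46 |
| 0.5 | 0.6 | 0.92 | 0.67 |
| 0.4 | 0.8 | 0.47 | 0.34 |

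Repeat runs agree within a few points; at 0.4/0.6 they gave 0.74 against 0.45 to 0.50. As a hand check at 0.4/0.6, the slope's standard error is 0.6 / (0.5 × √70) = 0.143, z = 0.4 / 0.143 = 2.79, and power is about Φ(2.79 − 1.96) = 0.80. That is close to the simulated value; the normal approximation runs slightly high.

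At slope 0.9 (step 2 settings), power is about 1.00 with continuous HbA1c and 0.81 to 0.94 with the cut.

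**Step 4: precision of the required amount.** In the 0.4/0.6 case at baseline 7.5%, the amount for a 50% chance solves 7.1 + 0.8 × 0.5 − 0.4 × (min/60) = 7.0, so min = 60 × 0.5 / 0.4 = 75 min/week. The 5th to 95th percentile range of the estimate was 56 to 108 min/week with continuous HbA1c and 42 to 142 with the cut.

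Share of trials with a finite 95% Fieller interval, both models adjusted, baseline mean 8.0, N = 70 (500 trials per setting):

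| Slope | Residual SD | Continuous | Cut at 7% |
|---|---|---|---|
| 0.3 | 0.5 | 66% | 21% |
| 0.3 | 0.8 | 33% | 13% |
| 0.5 | 0.5 | 96% | 65% |
| 0.5 | 0.8 | 70% | 37% |
| 0.9 | 0.5 | 100% | 99% |
| 0.9 | 0.8 | 99% | 86% |

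**Step 5: does the result depend on conditions ideal for linear regression?** At 0.4/0.6, power was 0.78 against 0.58 with skewed errors and 0.63 against 0.46 with unequal variance. With a curved dose relation it was 0.32 against 0.18. The gain remained in each.

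**The case against.** The strongest reply is that nothing binding is wrong. The logistic model is an example in an open exploratory section, technical detail is left to a separate SAP, and a continuous model is already allowed. That stands: a reader might infer that the Protocol commits the trial to the binary analysis, and it does not. The example is nevertheless the only method written for this aim, and so the likely default.

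Second, the cut follows from the clinical question, and logistic regression estimates the chance of reaching 7% directly, whereas the continuous route relies on linearity and residual shape. That is a real but small trade-off. Both can be checked on the data, and empirical residuals avoid assuming normality.

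Third, a reader might infer that most of the information is always lost. From the cut alone that is true only once the split is about 20/80 or more extreme.

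Fourth, a reader might infer that 70 patients cannot give a usable figure. That depends on values the Protocol does not state, and it fails at slope 0.9. At slope 0.3 the baseline-adjusted continuous model also gave an interval no wider than 60 min/week in only 0 to 7% of trials, so the sample size is part of the problem.

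Finally, the section sets no test or power target, so nothing indicates that a weak result would be reported as no relation. Power is used here only as a measure of information about the slope.

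**Conclusion.** The point holds as an improvement to an exploratory analysis. The illustrated model discards about a third to a half of the information through the cut alone, at splits from 50/50 to 20/80. With baseline HbA1c in both models, the loss against a continuous regression is about half or more.

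At N = 70, slopes of 0.3 to 0.5% per 60 min/week and residual SD 0.6, that means slope power of about 0.5 to 0.9 against 0.3 to 0.67, and a less precise required amount. The benefit lies in this moderate range. The sizes rest on assumed slopes, SDs and spread of walking; the direction was the same in every setting tried.

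Severity: consider. The aim is exploratory, appears only in the background, and the primary analysis is unaffected.

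**What to change.** In section 11.2.3 2), or in the SAP, make the illustrated model a linear regression of continuous week-20 HbA1c on weekly fast-walking time and baseline HbA1c. From the fitted mean and the empirical residuals, derive the probability of HbA1c below 7% at a given walking time and baseline, and the walking time for a given probability, with bootstrap or Fieller intervals. State that an unbounded interval will be reported as such. Keep the logistic model on below 7% as a supportive analysis, and check linearity and residual shape on the data.

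The cost is a sentence or two and a little programming. No new data, visits or patients are needed.
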